### Ethics and approval

The UK National REC (West Midlands Black Country Research Ethics Committee, Nottingham) gave favourable approval for PRIME protocol V.2.0 on 28 June 2021 (ref: 21/WM/0091). All participating centres have gained local and ethical approvals prior to receiving a site initiation visit and approval by the sponsor to open for recruitment.

### Patient and public involvement

Patients and public members were involved in defining the research question, evaluation of the research proposal, suggesting modifications to the trial, reviewing the patient information sheet, consent form and general practitioner letter. Patient groups and charities will also be involved in the dissemination of results.

### Consent

The clinical teams managing patients with suspected PCa who are referred to their centre will identify potential trial participants. Patient information sheets will be provided to patients. Members of staff who are trained to obtain informed consent, as indicated by the principal investigator (PI) on the delegation log for that site, will obtain the informed consent. A model patient information sheet is shown in online supplemental appendix 3.

10.1136/bmjopen-2022-070280.supp3Supplementary data

### Confidentiality

The data of the participants will be recorded into the eCRF system and analysed without any personal identifiers by pseudoanonymised coded information. A site’s source documents and identification lists will be archived in a secured facility at that centre.

### Dissemination

Results of this trial will be disseminated through national and international conferences and papers. Authorship criteria will be based on recommendations of the International Committee of Medical Journal Editors. The participants and relevant patient support groups will be informed about the results of the trial.

### Access to data

Only authorised individuals within the PRIME Clinical Operations Group have access to the final data set. Individual PIs have access to their own data but not that of other sites.

**WHO Trial Registration Dataset**

Please see table 4 for the WHO trial registration dataset.

**Table 4 T4:** WHO trial registration dataset

Data category	Information
Primary registry and trial identifying number	ClinicalTrials.gov: NCT04571840
Date of registration in the primary registry	1 October 2020
Sources of monetary or material support	Prostate Cancer UK. The John Black Charitable Foundation. European Association of Urology Research Foundation. The Dieckmann Foundation.
Primary sponsor	University College London
Secondary sponsor(s)	N/A
Contact for public queries	[name] [contact] Division of Surgery and Interventional Science, University College London, [name]
Contact for scientific queries	[name] [contact] Division of Surgery and Interventional Science, University College London, [name]
Public title/short title	Prostate Imaging Using MRI +/- Contrast Enhancement
Acronym	PRIME
Scientific title	A trial assessing whether bpMRI is non-inferior to multiparametric MRI in the diagnosis of clinically significant PCa
Countries of recruitment	Argentina Australia Belgium Brazil Canada Denmark France Finland Germany Italy The Netherlands Singapore Spain UK USA
Health condition or problem studied	Prostate neoplasm
Interventions	Device: MRI Diagnostic test: multiparametric MRI±prostate biopsy. Diagnostic test: bpMRI±prostate biopsy.
Intervention description	Active comparator: mpMRI. MRI with T2W, DWI and DCE followed by prostate biopsy if indicated on MRI and clinical findings. Diagnostic test: mpMRI±prostate biopsy. Experimental: bpMRI. MRI with T2W and DWI followed by prostate biopsy if indicated on MRI and clinical findings. Diagnostic test: bpMRI±prostate biopsy.
Key inclusion and exclusion criteria	Inclusion criteria Men at least 18 years of age referred with clinical suspicion of PCa. Serum PSA ≤20 ng/mL. Fit to undergo all procedures listed in the protocol. Able to provide written informed consent. Exclusion criteria Prior prostate biopsy. Prior treatment for PCa. Prior prostate MRI on a previous encounter. Contraindication to MRI. Contraindication to prostate biopsy. Unfit to undergo any procedures listed in the protocol.
Study type	Interventional Allocation: non-randomised Intervention model: single group assignment Intervention model description: within-person controlled, paired cohort, diagnostic evaluation study; participants undergo two index tests and a reference test Masking: single (care provider) Masking description: Radiologist assessing MRI for suspicion of PCa is blinded to the contrast sequence when reporting the bpMRI. After this report, they are unblinded to the contrast sequence and report the multiparametric MRI. All biopsies conducted as a result of MRI findings will be labelled as bpMRI and mpMRI, and diagnostic accuracy will be assessed against histological findings.
Date of first enrolment	5 April 2022
Target sample size	500
Recruitment status	Recruiting
Primary outcome(s)	Proportion of men with clinically significant cancer
Key secondary outcomes	Proportion of men with clinically insignificant cancer (Gleason score 3+3/Gleason grade group 1). Agreement between bpMRI and mpMRI for score of suspicion. Proportion of bpMRI scans and mpMRI whose quality was deemed adequate for reporting. Agreement between bpMRI and mpMRI for radiological staging decision. Agreement between bpMRI and mpMRI for treatment eligibility. Test performance characteristics for bpMRI and mpMRI when using the Likert scoring system in comparison to the PI-RADS scoring system. Proportion of men with clinically significant cancer missed by bpMRI and mpMRI-targeted biopsies and detected by systematic biopsy. Cost-effectiveness of bpMRI compared with mpMRI (cost per diagnosis of PCa).

bpMRI, biparametric MRI; DCE, dynamic contrast-enhance sequence; DWI, diffusion-weighted sequence; mpMRI, multiparametric MRI; PCa, prostate cancer; PRIME, Prostate Imaging Using MRI±Contrast Enhancement; T2W, T2-weighted sequence.

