**Figure 1 F1:**
[figure not shown]
The Prostate Imaging Using MRI±Contrast Enhancement trial schema—the approach prior to MRI. *indicates a 1–5 scale of suspicion for the likelihood that clinically significant PCa is present, with 5 representing the greatest score of suspicion. For MRI to be non-suspicious it needs to be scored 1 or 2 on both Likert and PI-RADS V.2.1 systems. For MRI to be suspicious it can be scored 3, 4 or 5 on either Likert or PI-RADS V.2.1 systems. bpMRI, biparametric MRI; DCE, dynamic contrast-enhanced sequence; DRE, digital rectal examination; DWI, diffusion-weighted sequence; mpMRI, multiparametric MRI; PI-RADS, Prostate Imaging Reporting and Data System; PSA, prostate-specific antigen; T2W, T2-weighted sequence.

The MRIs and lesions are scored on a 1–5 scale of suspicion for the likelihood that clinically significant PCa is present, with 5 representing the greatest score of suspicion. Both the traditional Likert and PI-RADS V.2.1 scoring systems will be used to identify any suspicious lesions in the prostate. Suspicious areas (Likert or PI-RADS V.2.1 score ≥3) on either bpMRI or mpMRI will undergo targeted biopsy of the prostate, with cores from contrast-enhanced suspicious areas stored separately.

A summary of the rules for reporting MRI scans in the PRIME trial is listed in box 2. Please see online supplemental appendix 1 for our model reporting proformas, which radiologists participating in the PRIME trial will use to label lesions.

10.1136/bmjopen-2022-070280.supp1Supplementary data

Box 2Summary of MRI reporting rules

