**bpMRI negative, mpMRI positive.**
There are two instances in which *new targets* may be labelled and drawn onto report 2:
*New* lesions scoring 3, 4 or 5, identified by DCE not previously identified on bpMRI should be marked on as new lesions as *DCE targets* and *bpMRI negative, mpMRI positive*.Lesions that appear *larger* on DCE should be treated as two separate targets.One target depicts the completely overlapping segment from report 1 (bpMRI positive, mpMRI positive).The non-overlapping part which would otherwise not be sampled should be labelled as a *new target* (bpMRI negative, mpMRI positive). This is a subjective decision by the radiologist. A typical example of when to declare this as a separate target is if the non-overlapping part enters an adjacent sector on the PI-RADS V.2.1 sector diagram.A biopsy plan is recommended by the radiologist thereafter for the biopsy operator to follow.

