### Prostate biopsy procedures

#### MRI-targeted biopsy

Men will undergo MRI-targeted biopsy if either their bpMRI or mpMRI identifies a suspicious lesion which scores ≥3 on either Likert or PI-RADS V.2.1. Four targeted cores will be taken per suspicious lesion, and these should be stored and labelled in separate containers to ensure cancer detection from separate suspicious areas is ascertained.

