#### Prostate histopathology

Both the Gleason score and the Gleason grade group will be reported for the overall biopsy and for each individual target lesion.

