#### MRI and pathology quality control

Quality control will be carried out at the end of the study by the PRIME chief radiologists reviewing the original MRIs, who will assess the MRI quality and re-report the MRI blinded to the study reports. Anonymised pathology slides from a proportion of patients may also be reviewed by central pathologists. Any slides assessed outside of the originating site will be returned to the original site after quality control. Quality control results will be reported but will not influence patient management or outcomes.

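### The registration entry has biopsies labelled by test and masks only the reporting radiologist, so the pathologist who grades the primary outcome may know which test produced each target

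*Protocol article*

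**What the plan says.** Table 4, under study type, defines the masking: "Masking: single (care provider) Masking description: Radiologist assessing MRI for suspicion of PCa is blinded to the contrast sequence when reporting the bpMRI". It goes on to state that the radiologist is then unblinded and reports the mpMRI, and that "All biopsies conducted as a result of MRI findings will be labelled as bpMRI and mpMRI, and diagnostic accuracy will be assessed against histological findings". Nobody else is listed as masked.

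The body of the article describes the chain from report to grade:

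- **Report 2 (Box 2).** Each lesion is classed as positive or negative on bpMRI and on mpMRI, and new contrast findings are marked as DCE targets. Then: "A biopsy plan is recommended by the radiologist thereafter for the biopsy operator to follow".
- **Reporting of MRI.** Targeted biopsy is taken "with cores from contrast-enhanced suspicious areas stored separately".
- **MRI-targeted biopsy.** Cores are kept apart by lesion: "these should be stored and labelled in separate containers to ensure cancer detection from separate suspicious areas is ascertained".
- **Prostate histopathology.** "Both the Gleason score and the Gleason grade group will be reported for the overall biopsy and for each individual target lesion". Under Primary outcome analysis, these grades determine whether a man counts as a detection for bpMRI, mpMRI or both.
- **MRI and pathology quality control.** "Anonymised pathology slides from a proportion of patients may also be reviewed by central pathologists". The same section says that quality-control results do not influence outcomes.

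No section says whether the pathologist or the biopsy operator knows which test identified a target.

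**The concern.** The primary comparison is paired within men. A lesion positive on both tests counts for both, so its grade cannot create a difference. A man contributes to the difference only if his significant cancer is found solely in a target belonging to one test. Those are the targets that a bpMRI/mpMRI label would give away.

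The boundary between Gleason 3+3 and 3+4 is a matter of judgement, and it is also the boundary of the primary outcome. A pathologist who expects contrast to add something, or expects it to add nothing, could lean either way on a borderline core from a contrast-only target. If more of these cores are called 3+4, bpMRI looks worse. If fewer are, bpMRI looks better and non-inferiority is easier to claim.

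Elsewhere the protocol guards against knowledge of the contrast series. Box 2 requires the blinding for report 1 to be verified by an independent person or an automated system, and the MDT first records treatment eligibility blinded to DCE. The grading step, which produces the primary outcome, has no stated equivalent. Central pathology review is optional and partial and leaves outcomes unchanged, so it could reveal a problem but not repair the result.

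**Working it through.** **The plan's own figure.** The Sample size section needs 400 evaluable men and allows for 20% dropout: 400 / (1 - 0.20) = 500, as stated. The margin is 5 percentage points, judged by the lower bound of the 95% CI. The point at issue is not a numerical error in the plan; the figures below only show how many men would matter.

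**Inputs.** N = 400, margin -5 points and mpMRI detection 38% come from Sample size. Let b be the number of men with significant cancer by mpMRI only, and c the number by bpMRI only. The documents give neither count, so both are assumed.

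**Formulas** (Wald interval for a paired difference):

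- d = (c - b) / N
- SE = √[(b + c) - (c - b)²/N] / N
- lower bound = d - 1.96 × SE

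**Base case, b = 12 and c = 4.** d = -8/400 = -2.0 points. SE = √(16 - 64/400)/400 = √15.84/400 = 0.00995. Lower bound = -2.0 - 1.95 = -3.95 points: pass.

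**Four more mpMRI-only men, b = 16 and c = 4.** d = -12/400 = -3.0 points. SE = √(20 - 144/400)/400 = √19.64/400 = 0.01108. Lower bound = -3.0 - 2.17 = -5.17 points: fail. Read backwards, four borderline grades withheld from contrast-only targets would turn this fail into a pass.

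**Four fewer, b = 8 and c = 4.** d = -1.0 point, lower bound -2.69: pass, and further from the margin. Starting here, 8 extra mpMRI-only men (b = 16) would be needed to fail.

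**Where the verdict flips.** The largest b that still passes is 13 with c = 0, 15 with c = 4, and 18 with c = 8. Each man moves d by 1/400 = 0.25 points.

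**Is the base case plausible under the plan?** At 38% detection, mpMRI finds 0.38 × 400 = 152 men and leaves 248. With b = 12 and c = 4, bpMRI finds 152 - 12 + 4 = 144 and leaves 256. The plan's probability A is then 12/256 = 4.7% and its probability B is 4/248 = 1.6%. Both lie within the planned range of 0 to 0.05, with A greater than B.

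From these two starting points, 4 to 8 men (1% to 2% of 400) regraded in one direction would change the conclusion.

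**The case against.** **The label may never reach pathology.** The Table 4 sentence is one line of a registry dataset and can be read as attributing results to each test in the data, which the paired analysis needs. The container rule asks only for separation by lesion, and neutral numbers would satisfy it. Biopsy detail is left to supplemental appendix 2, which is not shown, so coded labels cannot be excluded. This stands, and it limits confidence to moderate. It does not remove the point: the only wording shown specifies labels by test. If coded labels are in use, that wording misdescribes the procedure and should be corrected.

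**The operator is also unmasked.** A reader might infer that operator masking is a comparable, fixable gap. The documents do not support that. The operator follows the radiologist's plan, a contrast-only lesion can be recognised from the images, and under Box 2 a lesion larger on DCE becomes two adjacent targets, which reveals the origin of the second. Operator masking is largely unworkable here; its absence is a limitation to state.

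**The trial does mask others.** The MDT and the quality-control radiologists are blinded for their own tasks. That is correct, but neither step protects the primary outcome.

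**An inflated error rate.** A reader might infer a quantified rise in false non-inferiority. Simulation with true cells of 6% mpMRI-only and 1% bpMRI-only does move that rate from about 4% to about 16% if 4 of the expected 24 mpMRI-only detections are lost. No document supports a loss of one in six, all in one direction. Those cells also exceed the planning range: A = 0.05 with B = 0 gives 0.05 × 0.62/0.95 = 3.3%, about 13 men in 400 rather than 24. The figure shows sensitivity and does not estimate bias.

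**Conclusion.** The point holds in a limited form. The protocol article specifies biopsies labelled by test, describes masking only for the radiologist's first report, and nowhere masks the pathologist whose grades form the primary outcome. Whether the pathologist sees the label is an inference from this text, held with moderate confidence.

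The documents do not show that grading was biased, or in which direction it would go. Any effect would have to come through discordant targets, where small numbers decide the result: with 12 against 4 discordant men assumed, 4 regraded men take the lower bound from -3.95 to -5.17 points and reverse the conclusion. This rests on 400 evaluable men, a Wald interval, assumed discordant counts, and regrading that runs entirely one way.

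**What to change.** - Give every target a neutral number, in an order unrelated to which report found it, and use only that number on containers and pathology requests.
- Keep the mapping from target number to bpMRI/mpMRI status in report 2 and the eCRF. Each core stays traceable to its lesion, so the paired analysis loses nothing.
- Amend the masking description in Table 4 to say that the pathologist is masked to which sequence identified each target. If coded labels are already in use, correct the labelling sentence to say so.
- State as limitations that the biopsy operator is generally not masked, and that any men processed under test-based labels were graded without masking.

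The cost is a small change to forms and labels, with no extra staff or procedures and no change to patient care.

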### Current Protocol Version

The current protocol is V.2.0, issued 27 April 2021. The current protocol amendment number is 01. For full amendment history, please see table 5.

**Table 5 T5:** Revision chronology for amendments to protocol

Protocol version to date	Reasons for amendments
V.1.0, issued 24 August 2020	Original protocol
V.2.0, issued 27 April 2021	Main reasons for amendment: minor changes to make existing trial documents clearer. Main changes: Updated Section 18 Record Keeping and Archiving. Added the sentence, ‘Identifiable data will be kept by the site for 10 years, and non-identifiable data will be kept for a minimum of 20 years’. Version number and date added to all pages.

### Roles and Responsibilities

Please see table 6 for roles and responsibilities of the trial sponsor and involved committees.

**Table 6 T6:** Roles and responsibilities in the prime trial

Role	Details and responsibilities
Trial sponsor	University College London (UCL) Sponsor’s Edge reference: 135 819 Email: [contact] The trial sponsor did not provide any funding for the study. UCL has the role of research governance sponsor of PRIME. UCL adopted the study as sponsor after the UCL CCTU carried out a trial adoption process which involved the UCL CCTU reviewing the protocol to ensure it conformed to high standards of trial conduct and met the governance requirements of UCL. The UCL CCTU is responsible for oversight of the trial. The sponsor plays no role in data collection, management, analysis and interpretation of data, writing of the report or the decision to submit the report for publication.
PRIME operations group	The PRIME operations group consists of the CI, the Clinical Operations Group, National Cancer Imaging Translational Accelerator, the UCL Surgical and Interventional Trials Unit and the electronic case report form database managers. This group is responsible for Study planning. Preparation of protocol and revisions. Assistance with international review board/independent ethics committee applications. Preparation of investigators brochure and CRFs. Organisation of steering committee meetings. Provide annual progress reports to the ethics committee. Reporting serious adverse events to the sponsor and ethics committee when necessary. Responsible for trial master file. Budget administration and contractual issues with individual centres. Advice for PIs. Site initiation visits. Data verification and management. Central monitoring and resolving data queries with clinicians and nurses at the trial sites. Maintenance of the trial information technology system. Publication of study reports.
PI	At each participating site, the PI is responsible for the conduct of the clinical trial to ensure the safety of participants and the reliability and robustness of the data generated. They will be responsible for identification, recruitment, data collection and completion of CRFs, along with follow-up of trial patients and adherence to trial protocol. The PIs as leader of the research team may delegate their duties to members of their team.
Global TSC	The NCITA global prostate TSC is responsible for the governance of the PRIME study, and they have delegated safety to a DMSC. Roles and responsibilities To act as the oversight body for up to five prostate cancer studies on behalf of the sponsor and funders. In addition, the independent members will form a subcommittee to review safety. The role of the TSC is to provide oversight for the studies and provide advice through its chair to the CIs, work in tandem with the DMSC, sponsor, funders and host institution on all aspects of the studies. The rights, safety and well-being of the study participants are the most important consideration and should prevail over the interests of science and society.

CCTU, Comprehensive Clinical Trials Unit; CI, chief investigator; DMSC, data monitoring subcommittee; PI, principal investigator; TSC, trial steering committee; UCL, University College London.

## Data Availability

Data sharing not applicable as no datasets generated and/or analysed for this Protocol.
